# The place of S-ketamine in fibromyalgia treatment (ESKEFIB): study protocol for a prospective, single-center, double-blind, randomized, parallel-group, dose-escalation controlled trial

**DOI:** 10.1186/s13063-021-05814-4

**Published:** 2021-11-27

**Keywords:** S-ketamine, Fibromyalgia, Chronic pain, Treatment, N-Methyl-D-aspartate receptor

## Abstract

**Background:**

Fibromyalgia is a chronic multidimensional pain disease with no curative treatment currently available. Its management relies on a multimodal approach involving pharmacologic and non-pharmacologic elements. Because a suggested factor in its etiology is a central sensitization phenomenon involving the N-methyl-D-aspartate receptor (NMDAR), NMDAR antagonists have been proposed as a treatment target. Ketamine and its levogyre form, S-ketamine, have been used to treat chronic pain for many years without consensus about their therapeutic efficiency. We aim to assess the efficacy of S-ketamine as a co-treatment for fibromyalgia.

**Methods:**

This prospective, randomized, single-center, double-blind, parallel-group, dose-escalation trial will compare a co-treatment with S-ketamine (intervention) to a control treatment without S-ketamine (control). It will consist of two successive cohorts with 2:1 randomization ratio (S-ketamine at two different doses: control) with 105 participants in each cohort. The protocol follow-up time will be 12 weeks, including 3 visits for the treatment (week 0, week 2, and week 4) and 3 visits for follow-up (week 6, week 9, and week 12). Our primary outcome, pain relief and/or better patient function, will be assessed with the Brief Pain Inventory questionnaire. The statistical analysis will be performed on an intention-to-treat basis. If the primary outcome is reached at the end of follow-up in the first cohort with low-dose S-ketamine (0.2 mg/kg), the trial will end. If not, the trial will continue with the second cohort and high-dose S-ketamine (0.4 mg/kg).

**Discussion:**

The challenge of our trial is the inclusion of a large number of participants in comparison to other trials involving ketamine or S-ketamine infusions for chronic pain management. The originality of our protocol is to include functionality in addition to pain relief as a primary outcome because these two endpoints are not linked in a linear way. For some patients, functional status is more important than pain relief.

**Trial registration:**

EudraCT reference: 2020-000473-25, ClinicalTrials.gov: NCT04436250, first posted June 18, 2020; last updated July 21, 2020. Protocol version 2.2 issued on September 30, 2020, after a revision by the ethics committee. https://clinicaltrials.gov/ct2/show/NCT04436250

**Supplementary Information:**

The online version contains supplementary material available at 10.1186/s13063-021-05814-4.

## Background

### Rationale

Chronic pain is a multidimensional syndrome affecting 17–44% of the population of western countries [1, 2]. Fibromyalgia has been classified in the International Classification of Diseases as a primary chronic pain disease [3], with specific diagnostic criteria established by the American College of Rheumatology (ACR) [4]. Its prevalence in western countries varies from 0.7 to 3.3% [5, 6]. The condition leads to progressive deterioration in quality of life, as well as a reduction in relational and functional capacity, resulting in major personal and societal cost [4–6]. No curative treatment is currently available, and recent recommendations advise a multimodal approach combining pharmacologic and non-pharmacologic therapies with the objective of reducing pain and improving quality of life [7].

A central sensitization phenomenon has been proposed as one of the etiological mechanisms in fibromyalgia [8, 9]. This process has been defined by the International Association for the Study of Pain (IASP) as an “increased responsiveness of nociceptive neurons in the central nervous system to their normal or subthreshold afferent input” [10]. The N-methyl-D-aspartate receptor (NMDAR), located in the central nervous system, is a candidate factor in this process because its activation plays a major role in cognition, chronic pain, and neuroplasticity. Ketamine, a drug used for anesthesia since the 1970s, acts as a noncompetitive antagonist to NMDAR [11].

Ketamine has been hypothesized to provoke a “reset of the central nervous system,” reversing the deleterious effects of central sensitization. This drug thus has been proposed as a co-treatment for chronic pain involving central sensitization phenomena, such as fibromyalgia [11]. Ketamine exists as two stereoisomers: R-ketamine and S- ketamine. S-ketamine is about two to four times more potent than the racemic mixture, enabling lower dosage with the S- form for equianalgesic effects [12]. The advantage with the S-ketamine stereoisomer is in limiting psychotropic effects, fatigue, and temporary cognitive impairment compared with using the racemic mixture [13]. These characteristics are especially interesting for ambulatory administration.

Ketamine has been used in chronic pain treatment for as long as 20 years with various dosage and administration modalities, and consensus guidelines for its use have been established [11]. However, in a recent meta-analysis, Orhurhu et al. [14] observed that most studies assessing its efficacy are at high risk of bias, including small populations of patients. Many questions remain unanswered about the optimal dose of ketamine, frequency of administration, which diseases to target, and the real impact on patient functional status, in addition to pain relief. The authors of that meta-analysis call for new prospective randomized studies to address these questions [14], but to date, no recent large-scale study to our knowledge includes patients with fibromyalgia.

### Objectives

Our hypothesis is that S-ketamine, through its NMDAR antagonist properties, would improve the quality of life (pain reduction and/or functionality) of patients diagnosed with a fibromyalgia syndrome according to the ACR 2016 criteria and who exhibit the characteristics of a central sensitization phenomenon (Central Sensitisation Inventory (CSI) > 40) [15, 16]. If the results support our hypothesis, S-ketamine could have a role as a co-treatment for fibromyalgia in patients with central sensitization when recommended treatments remain unsatisfactory.

Our primary objective is to evaluate whether S-ketamine used as a co-treatment in chronic pain management will result in better pain control and/or in improvement of functionality in patients with fibromyalgia. We specifically target this double objective because pain relief and improved function are only partially linked: better pain relief does not always lead to improved functionality, and some patients prioritize a gain in function despite maintaining the same level of pain. In fact, studies have not been able to demonstrate a linear relationship between pain relief and gain of function [17, 18].

Our secondary objectives are to assess how S-ketamine used as a co-treatment affects quality of life, satisfaction, and emotional status, all of which are important in chronic pain syndromes.

## Methods/design

The trial respects the Guidelines ICH E6 for Good Clinical Practice (01/07/2002), the principles of the Helsinki declaration, the ICH E2A Guidelines (Clinical Safety Data Management: Definitions and Standards for Expedited Reporting), the European Union Clinical Trial Directive (2001/20/EC), and all Belgian legislation to maximize participant safety and protection.

Relative to the May 7, 2004, Belgian legislation concerning experimentation on human subjects, a no-fault insurance has been subscribed in the name of the Grand Hôpital de Charleroi, Belgium (GHdC).

### Trial design

This is a prospective, randomized, monocentric, double-blind, parallel-group, dose-escalation superiority study comparing an analgesic treatment including S-ketamine (intervention) to the same analgesic treatment without S-ketamine (control) (Fig. 1). The study design was inspired by Komen et al [19]. The dose-escalation design calls for a model with two successive cohorts, the first for comparing low-dose S-ketamine with the control treatment and the second cohort for comparing high-dose S-ketamine with the same control treatment.

**Fig. 1 Fig1:**
[figure not shown]
Trial design

This clinical trial is reported according to the Standard Protocol Items: Recommendations for Interventional Trials (SPIRIT) (see additional file 1).

#### Study setting

This study will be performed in the pain clinic of the GHdC, site Sainte-Thérèse, Charleroi, Belgium.

### Treatment

The intravenous route has been chosen for the administration of all drugs and provides 100% bioavailability and better reproducibility [11]. The different preparation steps are summarized in Fig. 2.

**Fig. 2 Fig2:**
[figure not shown]
Treatment preparation steps. ⏏, laminar flow hood; S-ket, S-ketamine; N°, recognition number; MgSO_4_, magnesium sulfate; Clo, clonidine; IMD, Investigational Medication Drug; NIMD, non-investigational medication drug

#### S-ketamine: investigational medication drug

Because this study is a dose-escalation type of study, we have chosen two dose regimens: low-dose S-ketamine at 0.2 mg/kg and high-dose S-ketamine at 0.4 mg/kg, both in kilograms of corrected ideal body weight according to the Lorentz formula [20]. These doses are subanesthetic and suitable and secure for ambulatory administration [21, 22]. They are consistent with equianalgesic ketamine doses recommended for pain treatment, as well as our current clinical practice [11, 14, 23].

S-ketamine will be prepared by the GHdC pharmacy, which will condition ampoules of S-ketamine (25 mg/ml) under a laminar flow hood into syringes of 2 ml containing 25 mg/ml of S-ketamine. Each syringe will have identical packaging with a recognition number linked to the randomization. These syringes will be sent to the pain clinic, where the responsible physician will prepare the right dosage of S-ketamine according to the patient’s weight and dilute it in physiological saline (0.9% NaCl) to obtain a volume of 45 ml. The product will be administered intravenously over 3 h (15 ml/h) with an electronic syringe pump.

#### Placebo

The placebo, physiological saline (0.9% NaCl), also will be prepared by the GHdC pharmacy, conditioned in syringes of 2 ml with identical packaging to those containing S-ketamine. Each syringe will have a recognition number linked to the randomization. These syringes will be sent to the pain clinic, where the responsible physician will prepare the placebo as if it were S-ketamine, diluting it in physiological saline (0.9% NaCl) to obtain a volume of 45 ml. This solution will be administered intravenously over 3 hours (15 ml/h) with an electronic syringe pump.

#### Control treatment: non-investigational medication drugs

All participants will receive a control treatment of magnesium sulfate 40 mg/kg, for antinociceptive effects [24, 25], and clonidine 1 μg/kg, an alpha-2 agonist acknowledged for analgesic effects. These doses are suitable for ambulatory treatment [26, 27]. Both drugs are used to achieve analgesia, so that even patients in the control group will experience an analgesic effect. The use of clonidine also is expected to alleviate any possible psychomimetic influence of S-ketamine. In fact, clonidine is among the low-dose benzodiazepines and alpha-2 agonists that are recommended for preventing or aborting ketamine-induced hallucinations or dissociation [11].

Pain clinic staff will prepare the control treatment according to the usual procedure. Magnesium sulfate 40 mg/kg (from 3 g/10 ml ampoules) and clonidine 1 μg/kg (from 150 μg/ml ampoules) will be administered together, diluted in physiological saline (NaCl 0.9%) to obtain a volume of 45 ml. The product will be administered intravenously over 3 h (15 ml/h) with an electronic syringe pump.

#### Regimen

Each patient will simultaneously receive an infusion of the control treatment and an infusion of the test drug (S-ketamine) or placebo, given via two different electric syringe pumps over the 3-h time period. Each participant will receive the treatment three times at 2-week intervals, which is consistent with our current practice and findings in the literature [14].

The trial’s follow-up time is 12 weeks and involves three visits for the treatment (week 0, week 2, and week 4) and three visits for follow-up (week 6, week 9, and week 12) (Table 1).

**Table 1 Tab1:** Summary of assessments, patient’s timeline

	Study period							
	Enrolment	Allocation	Post-allocation					Close-out
Timepoint	***T-2 weeks***	t-2 weeks ➔ t0	***T***_***0***_	***T+ 2 weeks***	***T + 4 weeks***	***T***_***+***_ ***6 weeks***	***T + 9 weeks***	***T + 12 weeks***
**Enrolment:**								
**Eligibility screen**	X							
**Informed consent**	X							
***Pregnancy test or electrocardiogram if needed***	X							
**Allocation**		X						
**Interventions:**								
***Treatment administration***			X	X	X			
***Follow-up consultation***						X	X	X
**Assessments:**								
***Central Sensitization Inventory (CSI)***			X					X
***EQ5D-5 L***			X					X
***Hospital Anxiety and Depression Scale (HADS)***			X					X
***Brief Pain Inventory (BPI)***			X	X	X	X	X	X
***Patient Global Impression of Change (PGIC)***			X	X	X	X	X	X
***Adverse events***			X	X	X	X	X	X

### Eligibility

#### Inclusion criteria

For inclusion, patients will be ages 18–65 years, consulting at the pain clinic of the GHdC, with chronic pain (as defined by the IASP) associated with fibromyalgia as defined by the ACR 2016 criteria [4], with a score > 40 on the CSI. They must also be eligible for intravenous ketamine ambulatory treatment according to our latest clinical practice, with no previous experience of treatment with ketamine or S-ketamine for fibromyalgia or other types of chronic pain. All participants will give written informed consent.

#### Exclusion criteria

Pregnant or breastfeeding women (based on patient questioning and urine pregnancy test for women of childbearing age) will be excluded. A pregnancy discovered during the study will be reported to the ethics committee. Women of childbearing age not using an approved contraceptive method with a safety rate > 99% (< 1% on the Pearl index) also will be excluded. Other exclusion criteria include a history of psychiatric disorders (e.g., psychosis), an inability to give informed consent (including because of a linguistic barrier), allergy or contraindication to any of the products used in the trial, and any medical condition or medication inconsistent with the study, based on the judgment of the clinical investigator.

### Definition of outcome measures

These outcomes have been chosen according to the IMMPACT (Initiative on Methods, Measurement, and Pain Assessment in Clinical Trials) recommendations [17, 18, 28].

#### Primary outcome

Our primary outcome is improvement in pain and/or functional status. Improvement will be defined as clinically significant as follows: for pain relief, a 2-point decrease in the Brief Pain Inventory (BPI) pain severity score [29], and for functionality, a one-point decrease on the BPI pain interference scale [28]. We will compare the proportions of patients with clinically significant improvement in each of these metrics between the S-ketamine and placebo groups.

#### Secondary outcomes

Our secondary outcomes are a 50% pain decrease on a numerical rating scale, impact on quality of life as evaluated using the EQ5D-5 L questionnaire, impact on emotional status using the Hospital Anxiety and Depression Scale questionnaire, and the incidence of adverse events solicited and spontaneously reported to the pain clinic staff. We also will assess patient global satisfaction with the treatment, as evaluated using the Patient Global Impression of Change questionnaire.

All questionnaires will be completed before drug administration, and during the follow-up visits together with secondary outcomes assessments (Table 1).

### Patient monitoring

All participants will be equipped with standard, non-invasive hemodynamic monitoring including heart rate, blood pressure, and oxygen saturation. The pain clinic staff, including a physician, will be present during the treatment administration. All adverse events will be monitored continuously and until resolution. If any expected adverse event occurs, it will be treated based on the incident management protocol (see additional file 2).

The patient will have access to a medical consult every 2 weeks for monitoring of pain status and medication adjustment as needed. Any standard treatment outside of the protocol that is relative to fibromyalgia (i.e., EULAR guidelines treatments) can be pursued during the study participation and adapted if necessary. The patient’s baseline treatment should remain the same from the beginning to the end of the protocol, as far as possible. The attending physician will evaluate the need to adapt the treatment if necessary for the patient’s wellbeing. All changes in baseline medication, if required, will be monitored and reported in the case report form.

All patients are free to discontinue the protocol at any time (which is part of the informed consent). Other criteria for study discontinuation for a participant will be lack of adherence to the protocol (for example not coming for the treatment) or serious adverse events.

### Missing data

Participants who do not present for one of the three treatment appointments or one of the three follow-up appointments will be excluded from the study and considered as lost to follow-up. To minimize missing data, pain clinic staff will supervise questionnaires’ completion, ensuring they are adequately filled.

In cases of missing data, we will analyze the cause, according to Rubin [30], and will test whether the data are missing completely at random, missing at random, or missing not at random. Multiple imputation (MI) for longitudinal data will be applied.

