### Sample size estimation

The sample size was calculated based on a cross-sectional sample of 25 patients already treated with ketamine (dose equivalent to 0.2 mg of S-ketamine), magnesium sulfate, and clonidine for whom we compared data before and 2 weeks after treatment. Applying our primary outcomes, we found that 28% (*n* = 7) met the pain relief objective and 56% (*n* = 14) met the functionality objective. Few data were found concerning a placebo effect, which we assessed at 10% under the conditions of our trial (data extrapolated from Noppers et al. [22]).

The selected size of the study population was calculated based on 0.8 (80%) power at an alpha of 0.0125. The alpha is set to 0.0125 because we will compare two primary outcomes twice, at most: the first comparison will be between the usual care+placebo treatment and usual care+low-dose S-ketamine treatment. If this comparison shows non-significant difference between the two groups, the second comparison will be between the usual care+placebo treatment and the usual care+high-dose S-ketamine treatment. Thus, for the primary outcome, a total of four comparisons will be made, so we divided the targeted *p* value (0.05) by this number of comparisons to arrive at a *p* value that allows for rejection of the null hypothesis of no difference observed between the groups. With a minimum clinically relevant difference of 5%, an expected rate of 10% improvement for the usual care+placebo group, and an expected rate of 25% improvement for the usual care+S-ketamine group, 55 patients per group are needed. Considering a drop-out rate of 20%, 70 patients per group will be needed to ensure that data for 55 per group will be available at the end of follow-up.

This number of patients for inclusion is ambitious, but the pain center treats more than 100 patients with fibromyalgia per year. The duration of recruitment is expected to be one year for the first dose cohort and one more year if a second cohort of patients is needed.

All patients will be recruited by the physicians of the pain clinic during their medical consult, according to the described eligibility criteria (Fig. 3).

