As noted, MI will be applied, using the mitml R package. Indeed, maximum likelihood and MI, using all available data in the study, will produce unbiased estimates of the treatment effect and correct *p* values. MI also is a method of choice because it allows for imputation of missing values on the outcome and on the covariate [35] and is valid for the three missingness categories (missing completely at random, missing at random, and missing not at random) [36]. Models obtained via maximum likelihood and MI will be compared. For continuous outcomes, we will look at the residuals of the model, and if these are not normally distributed, we will use the bestNormalize R package to transform the outcome and report the results of this last linear mixed model.

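### Excluding any randomised participant who misses one appointment conflicts with the intention-to-treat analysis and the planned imputation, and causes avoidable loss of week-12 data

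*Protocol article*

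**What the plan says.** The abstract of the protocol article (Methods) states: "The statistical analysis will be performed on an intention-to-treat basis".

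The Missing data section covers all six appointments. Participants who miss one of the three treatment visits or "one of the three follow-up appointments will be excluded from the study and considered as lost to follow-up". The next paragraph of that section says: "Multiple imputation (MI) for longitudinal data will be applied". The Statistical analysis section adds that "maximum likelihood and MI, using all available data in the study, will produce unbiased estimates of the treatment effect".

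The Patient monitoring section lists further grounds for ending a participant's study involvement: "lack of adherence to the protocol (for example not coming for the treatment) or serious adverse events". It does not distinguish between stopping the infusions and stopping data collection.

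The Sample size estimation section allows for losses: "Considering a drop-out rate of 20%, 70 patients per group will be needed". The purpose is to have 55 per group with data when follow-up ends. Table 1 schedules the BPI at all six visits (weeks 0, 2, 4, 6, 9 and 12) and places allocation before week 0.

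**The concern.** Intention-to-treat keeps every randomised patient in the assigned arm, whatever happens afterwards. A rule that excludes patients for a missed visit acts on an event after randomisation. On its face it reverses that principle.

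It also works against the missing-data plan. Staff supervise questionnaire completion, so missed visits should be the main source of missing BPI values. If those patients are no longer in the study, imputation has little left to act on beyond incomplete forms.

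Missed visits could plausibly differ by arm. The Blinding section accepts that dysphoric effects may let patients recognise ketamine, and the Patient monitoring section links leaving the study to non-attendance for treatment and to serious adverse events.

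The first cohort's result also decides whether the trial ends or goes on to a second cohort at the higher dose. An error in that comparison therefore affects the course of the trial as well as one estimate.

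**Working it through.** **1. The plan's own allowance.** Inputs from Sample size estimation: 55 evaluable per group, 20% drop-out.

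55 / (1 − 0.20) = 68.75, so 69. The plan states 70, which agrees to within one patient. (How the 55 was obtained is a separate matter and is not needed here.)

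Applied to one cohort of 105 at 2:1 (70 + 35), an equal 20% loss leaves 56 + 28 = 84. That is 21 randomised patients lost, with the control group falling from 35 to 28.

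**2. Share caught by the rule.** The rule counts six appointments. Because allocation precedes week 0, a randomised patient can miss any of the six. Let m be the chance of missing one visit (assumed) and let misses be independent (assumed). Share excluded = 1 − (1 − m)^6.

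- m = 2%: 1 − 0.98^6 = 11.4%
- m = 5%: 1 − 0.95^6 = 26.5%
- m = 10%: 1 − 0.90^6 = 46.9%

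Setting the share to 20% gives m = 1 − 0.80^(1/6) = 3.65%, about 3.7% per visit. If misses cluster within patients, the share excluded is smaller at the same m.

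**3. Reading A: excluded patients leave the analysis.** Let p be the true response rate in both arms (no effect), and suppose only non-responders are excluded, as a fraction d of the arm. The observed rate is then p / (1 − d). Assume d = 30% on S-ketamine and 5% on control.

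- p = 10% (the plan's control rate): 0.10/0.70 = 14.3% against 0.10/0.95 = 10.5%, a false difference of 3.8 points.
- p = 20% (assumed): 0.20/0.70 = 28.6% against 0.20/0.95 = 21.1%, a false difference of 7.5 points.
- p = 10% and d = 20% in both arms: 12.5% against 12.5%, no false difference.
- Exclusion unrelated to response within each arm: no bias, whatever the exclusion rates.

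The planned effect is 25% − 10% = 15 points. If the pattern of exclusion were reversed between arms, the sign of the bias would reverse too.

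**4. Reading B: earlier data kept, participation ends at the missed visit.** A patient who misses only week 2 then has no BPI at weeks 2, 4, 6, 9 and 12: five missing assessments instead of one. A patient who misses only week 6 loses three instead of one. Week 12 is lost in every case.

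Under the assumptions of step 2, the share without a week-12 BPI is m if collection continues and 1 − (1 − m)^6 under the rule. That is 2% against 11.4%, 5% against 26.5%, and 10% against 46.9%. The abstract judges the primary outcome when follow-up ends, so week 12 is the visit that matters most.

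**The case against.** The strongest reply is that nowhere does the article say these patients leave the analysis. Being lost to follow-up is a participant's status and does not define an analysis set. The rule stands under Missing data, directly before the imputation plan, and the Statistical analysis section refers to all available data. Reading B makes these statements compatible: the patient has no further visits, earlier data stay in, and later values are imputed. A rule that left imputation almost nothing to do would make part of the plan pointless, which counts against reading A.

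This stands to a large extent. A reader might infer that only patients with perfect attendance will be analysed, that week-12 data already observed will be thrown away, and that the comparison is therefore biased. The article establishes none of these. A patient excluded after a missed visit would normally not be seen at week 12, so the loss is of data never collected. Bias needs exclusion to be related to outcome, and the article gives no miss rates or patterns from which to estimate it.

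Two things remain. The text does not choose reading B either, and sizing the trial for 55 per group with data at the end leans towards reading A. And reading B does not rescue the rule, because it creates the missing data that imputation must then repair. A full protocol or SAP could define the analysis set more clearly, but it could not recover week-12 questionnaires that were never collected.

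**Conclusion.** The conflict is real and lies in the current text: exclusion for one missed appointment does not fit with intention-to-treat or with imputation from all available data. The rule needs changing on either reading. Under reading A, the comparison can be biased. Under reading B, obtainable week-12 BPI data are lost.

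The figures are illustrations. The share affected (11% to 47% for 2% to 10% missed per visit) rests on assumed miss rates and independence, and clustering would lower it. The false differences of 3.8 and 7.5 points rest on an assumed 30% against 5% exclusion of non-responders only. The lower figure uses the plan's own 10% control rate, and the bias is zero if exclusion is unrelated to outcome. It would go too far to say that the plan produces a biased result. It leaves open a route to bias and loses information that is cheap to keep.

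**What to change.** Amend the Missing data section to state that:

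- all randomised participants stay in the analysis set in their assigned arm;
- a missed appointment is a missing value at that visit only;
- BPI collection continues to week 12 after missed or stopped infusions, unless consent is withdrawn;
- lost to follow-up is reserved for participants from whom no further data can be obtained.

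In the Patient monitoring section, separate stopping study treatment from stopping data collection. The clinical rules for stopping treatment stay as they are. A completers analysis may be added as a sensitivity analysis, but this is optional.

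The cost is a short protocol amendment and some questionnaires by telephone or post for patients who do not attend.
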